### Concomitant Treatments

During the study period, the use of any psychotropic medications or other treatments for the target disorder is prohibited in principle, including psychotherapy and neuromodulation therapies (eg, transcranial magnetic stimulation). Medications for the management of treatment-emergent adverse events are permitted. Any concomitant medications or treatments used during the study, including those administered inadvertently, are documented in the case report forms, with details of drug name, dosage, dates of administration, and indication recorded at each visit. Participants who require initiation of prohibited treatments owing to clinical deterioration will be withdrawn from the study and will receive appropriate clinical care.

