### Study Procedure and Data Collection

Recruitment occurs at Peking Union Medical College Hospital through clinician referrals and community outreach. Following screening and provision of written informed consent, participants are assigned a unique alphanumeric study code (eg, IMT-1‐001). Eligible participants receive training on a custom-developed mobile app, which serves as the platform for collecting patient-reported outcomes and for delivering the daily musical intervention. Data acquisition encompasses six primary domains:

Demographics and history: age, sex, education, and detailed medical and psychiatric historySymptom severity: assessed using the Montgomery-Åsberg Depression Rating Scale (MADRS), Hamilton Anxiety Rating Scale (HAMA), Pittsburgh Sleep Quality Index (PSQI), Clinical Global Impression–Severity (CGI-S), and Immediate Mood Scale (IMS)Psychosocial functioning: evaluated via the Unified Psychophysiological-Psychosocial Assessment Questionnaire (UPPSAQ-70), Defense Style Questionnaire (DSQ), and Toronto Alexithymia Scale (TAS), etcNeurophysiology: includes optional assessments such as electroencephalography (EEG), functional near-infrared spectroscopy (fNIRS), MRI, and heart rate variability (HRV)Treatment credibility and expectancy: assessed at baseline (after allocation, before the first session) in studies 2 and 3 using the CEQ to permit measurement and statistical adjustment for expectation effectsSafety: monitored using the Young Mania Rating Scale (YMRS), the Brief Psychiatric Rating Scale (BPRS-4) positive symptom subscale, the UKU Side Effect Rating Scale, the Frequency, Intensity, and Burden of Side Effects Rating (FIBSER), and the Columbia-Suicide Severity Rating Scale (C-SSRS)

Follow-up visits occur at weeks 1, 2, 4, 6, and 8. These assessments focus on symptom severity, neurophysiology, and safety. At baseline in studies 2 and 3, participants additionally complete the Short Test of Music Preferences-Revised (STOMP-R). In study 4, baseline procedures include the application of the treatment-response prediction model derived from earlier datasets. For participants undergoing EEG, protocols include resting-state, P300, and mismatch negativity (MMN) paradigms. Additionally, a music-stimulation task (approximately 20 min of curated excerpts) is conducted at baseline and week 8 to characterize neural reactivity to the intervention.

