#### Secondary Outcome Measure

The secondary outcome is change in MADRS, HAMA, and PSQI scores.

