#### Primary Outcome Analysis

For the response rate at 8 weeks, between-group comparisons will be conducted using chi-square tests, with results reported as risk difference and risk ratio with corresponding 95% CIs. To accommodate the repeated-measures structure of the data (assessments at baseline and at weeks 1, 2, 4, 6, and 8), linear mixed-effects models for repeated measures (MMRM) will be used for continuous outcomes, with fixed effects for treatment group, time, and their interaction; baseline scores will be included as covariates; and random intercepts for participants will be specified to accommodate within-subject correlation. Because study 3 cannot blind participants and the IMT arm involves additional engagement, 2 prespecified sensitivity analyses will probe the robustness of the primary treatment effect to expectation and attention effects: (1) the MMRM and the response-rate models will be refitted with baseline CEQ scores added as covariates; and (2) the analyses will be repeated with adjustment for the Bang Blinding Index to explore whether the estimated treatment effect is attenuated after accounting for residual unblinding. Concordance between the primary (unadjusted) and these expectancy-adjusted estimates will be interpreted as evidence regarding the extent to which any observed benefit is attributable to personalization of the stimulus rather than to differential expectancy or attention. Time to response or remission will be compared between groups using Kaplan–Meier survival curves and the log-rank test. For study 3, the primary analysis will follow an intention-to-treat principle, including all randomized participants according to their assigned group. A supplementary per-protocol analysis will include only participants who complete at least 80% of scheduled listening sessions (ie, a minimum of 45 of 56 daily sessions).

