#### Missing Data

Missing data patterns will be examined and characterized as missing completely at random (MCAR), missing at random (MAR), or missing not at random (MNAR) using Little’s MCAR test and pattern analyses. Under the MAR assumption, multiple imputation by chained equations (MICE) will be used to generate 20 imputed datasets, and results will be pooled using Rubin’s rules. As a sensitivity analysis, last-observation-carried-forward (LOCF) imputation will be applied within the repeated-measures ANOVA framework, in line with our prespecified protocol. Additional sensitivity analyses under MNAR scenarios, including tipping-point analyses, will be conducted to evaluate the robustness of the findings.

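### Time to response or remission: if participants withdrawn for deterioration are censored, Kaplan-Meier overstates response, and more so in the arm that loses more of them

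*Protocol article*

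**What the plan says.** Under Plan for Statistical Analysis, Primary Outcome Analysis, the article fixes the method: "Time to response or remission will be compared between groups using Kaplan–Meier survival curves and the log-rank test". Under Concomitant Treatments it fixes what happens to certain treatment failures: "Participants who require initiation of prohibited treatments owing to clinical deterioration will be withdrawn from the study and will receive appropriate clinical care". The withdrawal is from the study, not only from the music. It applies to deterioration that leads to a prohibited treatment, not to every worsening.

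Study Procedure and Data Collection sets the observation times: "Follow-up visits occur at weeks 1, 2, 4, 6, and 8". The same analysis section says that for study 3 "the primary analysis will follow an intention-to-treat principle, including all randomized participants according to their assigned group". Missing Data adds "Under the MAR assumption, multiple imputation by chained equations (MICE) will be used to generate 20 imputed datasets" and "Additional sensitivity analyses under MNAR scenarios, including tipping-point analyses, will be conducted to evaluate the robustness of the findings". None of these sentences mentions time to response, and no section says how a withdrawn participant enters the survival analysis.

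Time to response is not among the listed outcomes. The primary outcomes are the 8-week response rate and EEG change, and for the rest "The secondary outcome is change in MADRS, HAMA, and PSQI scores".

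**The concern.** Kaplan-Meier and log-rank assume that a censored participant has the same later chance of the event as those still followed. A participant withdrawn because of deterioration has left for a reason that points away from response, and no later response can be observed. Censoring that person at withdrawal shrinks the risk set by someone unlikely to respond, so each later response counts for more.

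At stake are the reported cumulative response in each arm, and a between-arm P value under the Primary Outcome Analysis heading that could favour the arm in which more participants needed other treatment.

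**Working it through.** **No figure of the plan to reproduce.** The article gives no event count, hazard ratio, power or deterioration rate for this analysis. The inputs it does give are 70% control response and 50 per arm per diagnosis (Sample Size Calculation), hence 3 × 50 = 150 per arm pooled; visits at weeks 1, 2, 4, 6 and 8; and two-sided alpha .05.

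**Assumptions.** Withdrawal rates are scenarios. Responses fall at the five visits in the proportions .05/.15/.30/.25/.25, and deterioration withdrawals in the proportions .15/.20/.35/.30/0. Those withdrawn would not have responded.

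**Worked case: 70% response, 10% withdrawn, per 100 randomised.** Responders are 3.5, 10.5, 21, 17.5, 17.5; withdrawals are 1.5, 2, 3.5, 3, 0.

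- Censored at withdrawal, the numbers at risk are 100, 95, 82.5, 58, 37.5. The product of (1 − responders/at risk) is 0.965 × 0.8895 × 0.7455 × 0.6983 × 0.5333 = 0.238, so 1 − KM = 76.2%.
- Kept event-free to week 8, the numbers at risk are 100, 96.5, 86, 65, 47.5. The product telescopes to 30/100, so 1 − KM = 70.0%, the true value.

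**Range of scenarios.** SE = √(0.7 × 0.3/150) = 3.7 points.

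| Withdrawn | 1 − KM | Overstatement (points) | In SE |
|---|---|---|---|
| 2% | 71.1% | 1.1 | 0.3 |
| 5% | 72.9% | 2.9 | 0.8 |
| 10% | 76.2% | 6.2 | 1.7 |
| 15% | 80.1% | 10.1 | 2.7 |
| 20% | 85.0% | 15.0 | 4.0 |

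At 50% response the overstatement is 0.4 SE at 5% withdrawn and 0.9 SE at 10%.

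**Log-rank, same visit pattern, simulated with 150 per arm and equal 70% cumulative response.** Rejection is about 5% with 10% withdrawn in both arms, about 9% at 10% v 3%, about 17% at 15% v 5% and about 33% at 20% v 5%. Nearly all the excess favours the arm with more withdrawals. Keeping those participants event-free to week 8 restores about 5%.

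**Is the worse arm always made to look faster?** A second simulation had responses and withdrawals spread evenly over 8 weeks, 150 per arm. Arm A has more deterioration, and positive Z favours A:

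| True response A v B | Withdrawn A v B | 1 − KM A v B | Mean Z, censored | Mean Z, kept event-free |
|---|---|---|---|---|
| 70 v 70% | 20 v 5% | 0.85 v 0.73 | +1.6 | 0.0 |
| 60 v 70% | 20 v 5% | 0.72 v 0.73 | −0.5 | −1.7 |
| 50 v 70% | 15 v 5% | 0.56 v 0.73 | −2.8 | −3.5 |

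In the second row, the chance of showing B significantly faster is 7% with censoring and 41% without.

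A further case made deterioration independent of response, with equal response hazards and 20% v 5% deterioration. Log-rank was then about null (mean Z +0.1). But 1 − KM read 0.71 v 0.70, against true 8-week response incidence of 0.64 v 0.69.

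**The case against.** **No censoring rule is stated.** Kaplan-Meier and log-rank can be run with these participants kept in the risk set, so a reader who infers that the methods can only censor them goes too far. A condensed article may also leave the rule to the analysis plan. This stands as a limit on wording. It does not remove the point, because the article fixes both the method and the withdrawal rule, and the method's default gives the wrong answer.

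**Imputation might remove the censoring.** Response is a score threshold read at fixed visits. If missing scores were imputed and event times derived from them, nobody need be censored early. That is possible, but the Missing Data section does not extend imputation or tipping-point analyses to this analysis. The intention-to-treat sentence settles who is included, not what happens after withdrawal.

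**The rejection rates are not type I errors of log-rank's own null.** With censoring, the test compares the hazard of response among those remaining, and equal cumulative incidence with unequal withdrawal makes those hazards differ. This is correct. The figures show how often the test declares a difference when the proportions responding by each visit are the same.

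**The large effects need large imbalances.** Enrolment is limited to mild-to-moderate illness and follow-up lasts 8 weeks, so withdrawal may be rare. At 2 to 5% withdrawn the overstatement is under 1 SE, and equal withdrawal leaves the test near 5%. This stands and limits the importance of the point.

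**Conclusion.** The concern holds in a conditional form. If participants withdrawn for deterioration are censored at withdrawal, the censoring is informative. In every scenario tested, 1 minus Kaplan-Meier then overstated cumulative response in both arms, and more in the arm with more such withdrawals. When those withdrawn would not have responded, the log-rank comparison also moves towards that arm.

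A reader might infer that the arm with more deterioration will generally look faster. The calculations do not support that. It happens when true response is about equal; when that arm also responds less, its deficit is reduced or hidden; when deterioration is unrelated to response, log-rank is about null. A reader might also infer that the main response comparison is compromised. The week-8 response rate is compared by chi-square and is not affected by this route.

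The size depends wholly on withdrawal rates that the article does not give: minor at 2 to 5%, material at 10% or more, or where the arms differ clearly. It is a defect worth correcting in a supporting analysis.

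**What to change.** Add to the Primary Outcome Analysis section, after the sentence on Kaplan-Meier and log-rank: *For time to response and for time to remission, participants withdrawn for clinical deterioration or start of a prohibited treatment before the event remain in the risk set as event-free to week 8; only other losses are censored.*

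The alternative is to treat such withdrawal as a competing event, with Aalen-Johansen cumulative incidence curves and Gray's test. The two approaches are equivalent when the only other censoring is the end of follow-up at week 8.

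The change is statistical only and leaves the withdrawal rule as it is. It costs one sentence, needs the reason and date of withdrawal, and uses standard R software. The reported cumulative response becomes slightly less favourable. The quantity estimated becomes the cumulative incidence of response (or remission) by week 8, rather than the hazard among those who remain, and the text should say so.

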#### Missing Data

Missing data patterns will be examined and characterized as missing completely at random (MCAR), missing at random (MAR), or missing not at random (MNAR) using Little’s MCAR test and pattern analyses. Under the MAR assumption, multiple imputation by chained equations (MICE) will be used to generate 20 imputed datasets, and results will be pooled using Rubin’s rules. As a sensitivity analysis, last-observation-carried-forward (LOCF) imputation will be applied within the repeated-measures ANOVA framework, in line with our prespecified protocol. Additional sensitivity analyses under MNAR scenarios, including tipping-point analyses, will be conducted to evaluate the robustness of the findings.

#### Heterogeneity of Target Disorders, Subgroup Analyses, and Multiple Comparisons

Recognizing that MDD, GAD, and PI differ in symptom profiles and neurobiological mechanisms, the primary analysis of study 3 will pool all 3 disorders to maximize statistical power, with diagnostic group included as a stratification factor in the randomization and as a covariate in all pooled models. Treatment × diagnosis interaction terms will be included in the mixed-effects models to assess whether treatment effects vary by disorder. If significant heterogeneity is detected, disorder-specific results will be reported separately. The analytic hierarchy is specified a priori as follows. The pooled treatment effect (IMT vs nonindividualized therapy), adjusted for diagnosis, is the confirmatory primary contrast. Disorder-specific treatment effects (MDD, GAD, and PI analyzed separately) are prespecified secondary, hypothesis-generating analyses. For each disorder, we will report the response-rate difference and the MMRM-derived between-group difference in symptom change with 95% confidence intervals, regardless of statistical significance, so that the direction and precision of the per-disorder estimates are transparent and can inform the design of a future definitive trial. The treatment × diagnosis interaction will be evaluated primarily as a test of effect-modification rather than as a gatekeeper for reporting; disorder-specific estimates will be presented whether or not the interaction term reaches significance, but will be explicitly labeled exploratory. We acknowledge that this pilot is not powered for confirmatory subgroup inference. With approximately 50 participants per arm per disorder (100 per diagnostic group), each disorder-specific contrast has limited power to detect between-arm differences smaller than a large effect, and the trial is powered for precision of estimation rather than for hypothesis testing within subgroups (see Sample Size Calculation). To avoid over-interpreting unstable subgroup estimates, the disorder-specific analyses will be supplemented by a hierarchical Bayesian model in which disorder-specific treatment effects are treated as exchangeable and shrunk toward the overall pooled effect; this borrows strength across the 3 disorders and yields more stable, less extreme per-disorder estimates than fully separate analyses. Posterior means and 95% credible intervals for each disorder will be reported alongside the frequentist estimates. We will not draw definitive efficacy conclusions for any individual disorder from study 3; rather, the per-disorder estimates will be used to generate hypotheses and to inform stratified sample-size planning for the definitive trial. It should be noted that the music therapy protocol uses the same affective trajectory for participants with MDD and GAD, whereas a distinct biphasic trajectory is used for participants with PI. This difference in trajectory design reflects the distinct clinical objectives for each disorder and will be accounted for in the analysis by including trajectory type as a covariate in sensitivity analyses. Because trajectory type is collinear with the PI-versus-(MDD and GAD) distinction, this covariate adjustment will be reported as a sensitivity analysis complementary to the disorder-stratified analyses above. For the family of disorder-specific secondary contrasts, the false discovery rate will be controlled using the Benjamini–Hochberg procedure, and both adjusted and unadjusted *P* values will be reported.


#### Assumption Checks and Robustness

Assumptions for parametric analyses (normality and homogeneity of variance) will be assessed using the Shapiro–Wilk test, Q–Q plots, and the Levene test. When assumptions are not met, nonparametric or variance-robust alternatives will be applied. All analyses will adhere to a prespecified statistical analysis plan that will be finalized before database lock.

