#### Descriptive and Baseline Analyses

Continuous variables with approximately normal distributions will be summarized as mean (SD) and compared between groups using independent-samples 2-tailed *t* tests (with Welch correction when variances are unequal); nonnormally distributed continuous variables will be summarized as median (IQR) and compared using the Mann-Whitney *U* test. Categorical variables will be summarized as counts (%) and compared using chi-square tests (continuity-corrected for 2×2 tables) or the Fisher exact test when expected cell counts are below 5. Baseline demographic and clinical characteristics will be compared across groups to assess the adequacy of randomization in study 3, and baseline CEQ scores will be compared between arms.

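### Assumption checks on the outcome data may replace the named mixed models for the continuous outcomes (symptom-score and EEG change); those models should stay the main analysis whatever the checks show

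*Protocol article*

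**What the plan says.** Under Primary Outcome Analysis the model for the continuous outcomes is named: "linear mixed-effects models for repeated measures (MMRM) will be used for continuous outcomes, with fixed effects for treatment group, time, and their interaction". Baseline score is a covariate and participants have random intercepts. The section on heterogeneity and multiple comparisons adds diagnosis to every pooled model, adds a treatment-by-diagnosis interaction, and promises an MMRM-based difference with a 95% CI for each disorder whether or not it is significant. EEG Data Analysis names mixed-effects models for the EEG outcomes.

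Assumption Checks and Robustness then says: "Assumptions for parametric analyses (normality and homogeneity of variance) will be assessed using the Shapiro–Wilk test, Q–Q plots, and the Levene test". The next sentence is the rule at issue: "When assumptions are not met, nonparametric or variance-robust alternatives will be applied". The section closes with "All analyses will adhere to a prespecified statistical analysis plan that will be finalized before database lock".

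Two further places set the scope. The clinical primary outcome is binary: "For the response rate at 8 weeks, between-group comparisons will be conducted using chi-square tests". The only nonparametric two-group test named for continuous data is in Descriptive and Baseline Analyses: "nonnormally distributed continuous variables will be summarized as median (IQR) and compared using the Mann-Whitney" *U* test.

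**The concern.** The rule is stated text, not a gap left for the SAP. The MMRM and the EEG mixed models are parametric analyses, so the sentence reaches them on its natural reading. It lets the outcome data decide which analysis is reported. A later SAP could name the alternatives and the test level, but the choice would still depend on the data. A Levene test between arms also needs the allocation, so that trigger can be evaluated only once the data are split by arm.

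What is at stake is mainly the quantity estimated. Study 3 is sized for precision and is meant to supply effect estimates for a definitive trial. A rank comparison does not give an adjusted mean difference in symptom change. A simple rank test would also have no place for the baseline score, the repeated visits or the diagnosis term, and it would sit badly with the MMRM-based differences promised for each disorder.

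**Working it through.** The protocol gives no figure for how often the switch would occur, and no means, SDs or skewness for any scale. The only design inputs are N = 3 disorders × 2 arms × 50 = 300, the 70% control response rate used for sizing, and two-sided α = 0.05. Everything else below is an assumption.

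**1. What the rule can reach**
- Week-8 response rate (clinical primary): chi-square on a binary outcome, not affected.
- Change in MADRS, HAMA and PSQI (secondary): MMRM, affected.
- Quantitative EEG change (listed as primary, to be read as exploratory): mixed models, affected.

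**2. How often Shapiro–Wilk would reject at 0.05 (simulation)**

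| What is tested | n=300 | n=100 (one disorder) |
|---|---|---|
| Gamma data, skewness 0.2 | 22% | 10% |
| skewness 0.3 | 45% | 18% |
| skewness 0.5 | 89% | 44% |
| skewness 0.75 | 100% | 77% |
| Integer scores floored at 0, mean 12, SD 5 | 40% | 9% |
| mean 8, SD 5 | 100% | 65% |
| Week-8 residuals after baseline adjustment, mean reduction 40% to 50% | 9% to 10% | 7% to 8% |
| mean reduction 60% | 23% to 71% | 7% to 22% |
| mean reduction 70% | 99.8% | 69% |
| Three normal scales with unequal SDs, pooled | 15% to 74% | not run |

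The residual rows are the closest to the stated model. They use a single-visit ANCOVA in place of the MMRM, with baseline mean 20 and SD 4. Levene flagged about 4% to 5% at n=300, with equal spread built into both arms.

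The 70% response rate narrows this only with a further assumption. If percentage reduction is roughly normal with SD 20 to 30 points, then P(reduction ≥ 50) = 0.70 gives a mean of 50 + 0.524 × SD, which is 60.5 at SD 20 and 65.7 at SD 30. That points to the 60% rows and somewhat above them. A rerun of the two 60% scenarios gave response rates of 69% and 66% and rejection rates of 22% and 73%, in line with the table.

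**3. Type I error at n=300 (4,000 null trials at each residual skewness from 0 to 1.0)**
- Baseline-adjusted model always: 4.4% to 4.7%.
- Mechanical switch from Shapiro–Wilk to Mann–Whitney: 4.2% to 5.1%.
- Smallest P value among ANCOVA, ANCOVA with HC3 standard errors, and Mann–Whitney: 6.7% to 7.1%.

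The baseline-adjusted model keeps its error rate without a switch, so the switch is not needed for validity here.

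**4. Power if the fallback were Mann–Whitney on week-8 scores (assumed effect 0.3 SD, 150 per arm)**

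Unadjusted signal: 0.3 / √(2/150) = 0.3 / 0.1155 = 2.598. With baseline correlation r, power ≈ Φ(2.598/√(1−r²) − 1.96).
- r = 0.3: Φ(2.724 − 1.96) = 78%
- r = 0.5: Φ(3.000 − 1.96) = 85%
- r = 0.6: Φ(3.248 − 1.96) = 90%
- Mann–Whitney, normal scores: Φ(2.598 × √(3/π) − 1.96) = Φ(2.539 − 1.96) = 72%

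Simulation gave 77%, 85%, 90% and about 71%. An unadjusted comparison of means has Φ(2.598 − 1.96) = 74%, so most of the loss comes from dropping the baseline score and not from using ranks.

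**The case against.** The case on the other side is substantial, and it limits the point in five ways.

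- **Scope.** A reader might infer that the trial's deciding analysis is open. It is not: the response rate is compared by chi-square, which normality and Levene checks cannot touch. Symptom-score change is secondary, and EEG findings are to be read as exploratory. This stands.
- **Likelihood.** A reader might infer that with 300 participants the switch is close to certain. The documents give no score distribution, a responder proportion fixes neither skewness nor a floor, and simulated rejection ran from 9% to 100%. The rule also lists Q–Q plots beside the tests and states no P-value trigger, so a rejection need not mean a switch. This stands.
- **Fallback.** A reader might take Mann–Whitney as the replacement for the MMRM. The protocol names it only for simple group comparisons. The rule equally allows variance-robust methods, and these can keep baseline, visits and diagnosis. The power figures therefore describe only the least favourable permitted reading.
- **Reporting promise.** The promised MMRM-based estimates for each disorder mean that full replacement would contradict the text. This stands, but the promise does not expressly cover the pooled contrast.
- **SAP detail.** The alternatives, the test level and the data to be tested may be specified in the SAP, which is not shown, so their absence here is no fault. This stands too. It does not answer the remaining point, which is that the stated rule makes the choice of main analysis depend on the outcome data.

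**Conclusion.** The point holds in limited form. The protocol lets assumption checks on the outcome data replace the mixed models named for symptom-score change (secondary) and EEG change (listed as primary, read as exploratory). The primary response-rate analysis is unaffected.

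The harm is modest but real. Its main part is a possible change of estimand in a trial whose purpose is estimation. Error-rate inflation arises only if the choice among methods is free, and then reaches about 7%. The power loss, from 77%–90% to about 71%, applies only if the fallback is a rank test without the baseline score, and it rests on an assumed 0.3 SD effect and baseline correlations of 0.3 to 0.6. The type I results come from a single-visit ANCOVA standing in for the MMRM. The documents do not show how likely a switch is.

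**What to change.** In Assumption Checks and Robustness, replace the switching sentence with three statements:

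1. The mixed models named for symptom-score and EEG outcomes are the main analysis of every continuous outcome, whatever the assumption checks show, with robust (sandwich) standard errors from the outset.
2. Shapiro–Wilk, Q–Q plots and Levene results describe model fit and do not select the analysis.
3. Any rank-based analysis is a named sensitivity analysis that keeps baseline score and diagnosis, for example a rank ANCOVA at week 8.

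The cost is a short wording change carried into the SAP and one sensitivity analysis, with no new data. The downside is a very slight loss of efficiency when the model is exactly right.
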